#### **5.Interventions**

##### **(1) MITD-LaC procedure**

A 1.5 cm incision will be made at the distal end of the perineal anal fistula, and the subcutaneous tissue will be separated to expose the fistula. Following the path of the fistula, the fistula tract will be carefully dissected to the posterior anal margin, at which point a radial incision will be made. For complete HHAF, the same procedure will be performed, extending the dissection towards the contralateral anal margin until reaching the internal opening. Subsequently, the fistula will be excised, and all surrounding inflammatory and necrotic tissue will be

meticulously removed. The fistula located above the dental line will be incised, and an optical fiber guide wire will be placed into the upper portion of the fistula tract, followed by laser vaporization and ablation of the fistula tract. After achieving hemostasis and performing thorough wound irrigation, a rubber drainage tube will be carefully inserted between the adjacent incisions and firmly secured in position. The wall of the rubber drainage tube should be perforated with multiple small holes, each approximately 2mm in diameter, thereby optimizing drainage efficiency.

## (2) ITD procedure

The fistula tracts and abscess cavities located below the dentate line will be excised or excoriated, the wound margin will be debrided, and it will be ensured that any inflammatory and necrotic tissues within the tracts will be extirpated. At the same time, the fibrotic wall and scar tissue around the external opening should be removed completely. A radial incision will be made about 3cm on the anal margin at the internal opening position, followed by incision and curettage of the fistula tract to remove any necrotic tissue and completely excise both the internal opening and associated infectious lesions. After open drainage of the wound, a probe will be inserted into the internal opening and guided out through the anus. A rubber band will be then attached to the end of the probe and pulled out of the anus. Subsequently, the two ends of the rubber band should be pulled tightly and then fixed with silk thread. The wound margin will be trimmed, and then compression hemostasis and packing will routinely be performed. Subsequently, standard bandaging and fixation procedures will be carried out to secure the wound area.

## **6. Clinical observation index**

### (1) Baseline data statistics

Baseline information (such as gender, age, height, weight, primary/recurrent, etc.) will be

recorded for both groups before surgery.

## (2) Primary outcome measure

The primary outcome measure is wound healing time, defined as the duration from the day of surgery to complete epithelialization of the surgical wound[10]. Wound healing will be confirmed by the doctor's local examination and integrative evaluation during the patient's regular outpatient follow-up after surgery.

## (3) Secondary outcome measure

Secondary outcomes include the assessment of postoperative pain levels on days 1, 3, and 5 using a visual analogue scale (VAS). Additionally, the Cleveland Clinic Florida Incontinence Score (CCF-IS) will be employed to assess fecal incontinence scores within 30 days post-surgery. Postoperative complications, such as infection, urinary retention, bleeding, delayed wound healing, and recurrence within one month after surgery, will also be observed. Furthermore, the Quality of Life in Patients with Anal Fistula Questionnaire Score (QoLAF-QS) will be utilized to evaluate patients' quality of life six months following the operation.

The occurrence of postoperative infection is defined as the presence of obvious pain accompanied by swelling and pustulation at the surgical site, with or without fever, and necessitating administration of antibiotic therapy. Postoperative urinary retention is defined as the inability to void spontaneously in the presence of bladder overdistension, necessitating catheterization for relief[11]. Postoperative bleeding is defined as excessive bleeding that requires urgent management like local pressing hemostasis in the bleeding site[12]. Delayed wound healing is defined as any wound that has not achieved complete re-epithelialisation by 3 months[13]. Recurrence is defined as a fistula that reoccurs around the previous surgical site, and

often requires the utilization of TRUS or EMRI for diagnostic assistance[ 14, 15].

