## Abstract

**Introduction :** High horseshoe-shaped anal fistula (HHAF) is a complicated and challenging condition that presents considerable obstacles in treatment. We are presently investigating a novel surgical technique involving a combination of multi-incision and tube-dragging therapy, and laser closure (MITD-LaC) for the management of HHAF. Due to the current scarcity of rigorous evidence evaluating this approach, it is essential to perform a well-designed randomized controlled trial to compare the effectiveness of this new method with incision and thread-drawing therapy.

**Methods and analysis:** This trial is a prospective, randomized, controlled and interventional study. After preliminary screening of qualified outpatients, a total of 64 adult patients will be enrolled in the trial and randomly allocated to either the MITD-LaC group or the control group (n=32 per group). These patients will receive either MITD-LaC or incision and thread-drawing therapy. The design aims to allow for a robust comparison between the two treatment modalities. The primary endpoint is the wound healing time, while secondary endpoints include postoperative anal pain at 1, 3, and 5 days (measured with visual analogue scale), fecal incontinence score within 30 days after operation (measured with Cleveland Clinic Florida incontinence score), and the occurrence of postoperative complications within 1 month after surgery, and quality of life up to six months postoperatively (evaluated by The Quality of Life in patients with Anal Fistula Questionnaire Score).

**Discussion:** This study represents the first randomized controlled trial evaluating the short-term outcomes of MITD-LaC, thereby aiming to contribute high-quality evidence to guide clinical

practice. Moreover, this trial incorporates comprehensive outcome measures assessing both subjective and objective dimensions. Because of this multidimensional assessment, MITD-LaC offers a promising potential for broader application in the treatment of HHAF. Consequently, obtaining more definitive and authoritative evidence through scientifically rigorous clinical trials is of utmost importance in further validating this treatment approach.

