#### **4.Sample size estimation**

The sample size for this study is calculated using a two-sample comparison of means. Previous research has reported that the average healing time for patients treated with incision and thread-drawing therapy for HHAF is  $62.69 \pm 3.54$  days[9]. In our study, we assume a reduction in average healing time by 3 days in the MITD-LaC group, with an allowable error ( $\delta$ ) of 3 days and a known standard deviation of 3.54 days. The study is powered to an  $\alpha=0.05$  (type I error rate) and  $\beta=0.10$  (type II error rate), leading to  $Z_{\alpha}=1.960$  and  $Z_{\beta}=1.282$ , as determined from statistical tables. Based on the calculation, at least 25 participants are required for each group, as computed using Power Analysis and Sample Size Program 2021 (PASS, NCSS Statistical Software, Kaysville, UT, USA). To account for an anticipated dropout rate of 20%, we aim to recruit a total of 64 participants for both groups, thus allocating 32 participants per group.

Randomization will be performed using a random number table generated through SAS software, which will be based on the total number of cases. The treatment allocation will correspond to serial numbers Q01-64, creating an overall random code table. These numbers will be assigned in accordance with the order of outpatient visits.

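### Complications are counted only within one month of surgery, so delayed healing (defined at 3 months) cannot be classified in its window and recurrence cannot be meaningfully assessed in it

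*Protocol*

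**What the plan says.** Section 6(3), Secondary outcome measure, lists the complications and their window together: "Postoperative complications, such as infection, urinary retention, bleeding, delayed wound healing, and recurrence within one month after surgery, will also be observed". The abstract gives the same window for complications as a whole: "the occurrence of postoperative complications within 1 month after surgery".

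The definitions follow in section 6(3). For delayed healing: "Delayed wound healing is defined as any wound that has not achieved complete re-epithelialisation by 3 months". For recurrence: "Recurrence is defined as a fistula that reoccurs around the previous surgical site". The recurrence definition adds that ultrasound or MRI is often needed to help with the diagnosis. It sets no minimum time and does not require that the wound has healed first.

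Three other places bear on the point:

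- Section 6(2) makes wound healing time the primary outcome, "defined as the duration from the day of surgery to complete epithelialization of the surgical wound", confirmed by examination at regular outpatient follow-up. It does not say how long that follow-up lasts.
- Section 4 reports that the "average healing time for patients treated with incision and thread-drawing therapy for HHAF is" 62.69 ± 3.54 days, and adds: "we assume a reduction in average healing time by 3 days in the MITD-LaC group".
- Section 6(3) places a quality-of-life questionnaire at six months. No examination or imaging is stated for that contact.

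**The concern.** Delayed healing has a window that ends about two months before its own definition can be met. Recurrence has a window that ends, on the protocol's planning figures, about a month before the average wound has healed.

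The primary outcome measures closure of the surgical wound. Delayed healing and recurrence are the listed complications that bear most directly on whether that closure is achieved in reasonable time and whether it lasts. If the one-month rule were followed literally, the report would show no delayed healing in either arm, and a recurrence figure that says little about what happens after healing. Such figures could be read as evidence of durability that the trial did not collect. If the rule were not followed literally, the window would be chosen during conduct or analysis, possibly with the data in view.

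**Working it through.** The plan states no calculated figure on this point, so there is none to reproduce. The check compares the stated windows with the definitions and with the planning figures in section 4.

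**Step 1: delayed healing.** The window closes at about day 30 (one month, section 6(3) and abstract). The definition is met or not met at 3 months, about day 90 to 92. The gap is 90 − 30 = 60 days or slightly more. A wound open at day 30 is neither a case nor a non-case, because the definition looks at day 90. No patient can be classified as a case inside the window. This needs no distributional assumption.

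**Step 2: share of wounds healed by day 30.** Inputs from section 4: ITD mean 62.69 days; MITD-LaC mean 62.69 − 3 = 59.69 days; SD 3.54 days. A normal distribution is assumed.

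- ITD: (30 − 62.69)/3.54 = −9.2 SD
- MITD-LaC: (30 − 59.69)/3.54 = −8.4 SD

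On these figures essentially none of the 64 wounds would be healed by day 30.

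**Step 3: sensitivity to the SD.** An SD of 3.54 days may be too small, so larger values are assumed. They are not in the protocol. The expected count is 32 × (share in ITD + share in MITD-LaC).

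| Assumed SD (days) | Healed by day 30, ITD | Healed by day 30, MITD-LaC | Expected healed, of 64 |
|---|---|---|---|
| 10 | 0.05% | 0.15% | 0.1 |
| 15 | 1.5% | 2.4% | 1.2 |
| 20 | 5.1% | 6.9% | 3.8 |

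Even at an SD of 20 days, about 60 of 64 wounds would still be open when the window closes. A fistula found at the site in that period can hardly be distinguished from one that never resolved. A recurrence that follows healing at about day 60 falls outside the window.

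**Step 4: what the planning figures cannot show.** Applied at day 90, the same model gives (90 − 62.69)/3.54 = 7.7 SD above the ITD mean and (90 − 59.69)/3.54 = 8.6 SD above the MITD-LaC mean. It therefore predicts practically no delayed healing at 3 months either. With an assumed SD of 15 or 20 days, the share unhealed at day 91 is 3.0% or 7.8% with ITD and 1.8% or 5.9% with MITD-LaC. That is 32 × (0.030 + 0.018) = 1.5, or 32 × (0.078 + 0.059) = 4.4, patients of 64. The number of delayed-healing events lost to the one-month window is thus not known from the document. The case on delayed healing rests on Step 1 alone.

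**The case against.** **The one month may belong to recurrence only.** The sentence in section 6(3) can be parsed that way. The abstract does not allow it, because it attaches the month to postoperative complications in general. Even on the narrow reading, recurrence would still be confined to one month.

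**Recurrence does not strictly need a healed wound.** This stands. A reader might infer that recurrence is impossible inside the window, so that both rates are zero by construction, or 0 of 64 whatever the truth. The protocol does not support that for recurrence. Its definition sets no condition of prior healing and no minimum time, and it mentions imaging. A tract seen on imaging and epithelialisation of the skin are different observations. What remains is that the window is badly placed for recurrence, not that an observation is ruled out.

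**The delayed-healing data will exist anyway.** This is largely right. The primary outcome follows each wound to epithelialisation, so a wound open at 3 months should appear in that record, provided follow-up of unhealed patients reaches that point. The fault lies in the stated window, and a loss of data is not shown. It still needs correcting, because the rule as written excludes the events that the definition describes.

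**The trial is about short-term results.** The abstract does frame it so, and how far to pursue recurrence is partly a choice of scope. But the protocol itself lists both outcomes and defines one of them at 3 months. A short horizon is defensible for recurrence if it is declared and no conclusion is drawn beyond it.

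**The harm may be overstated.** A reader might go further and infer that a residual tract is the chief way in which MITD-LaC fails, and that faster closure is bought at that price. Nothing in the document says so, and the point does not depend on it.

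**Conclusion.** The point holds in two parts of different strength.

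Delayed healing cannot be classified within its stated window. This is a direct contradiction between the one-month window (abstract and section 6(3)) and the 3-month definition (section 6(3)). It rests on no assumption.

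Recurrence cannot be meaningfully assessed within one month. This rests on the section 4 planning means of 62.69 and 59.69 days and on approximate normality. It survives an SD more than five times the planned one (20/3.54 = 5.6), at which about 5% to 7% of wounds would be healed by day 30. It does not establish that recurrence would be zero.

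The fault affects two components of a secondary outcome. The primary outcome, the sample size and the randomisation are not touched by it. It should be corrected because, as written, one named outcome is unusable and the other is close to uninformative, and the correction for delayed healing is nearly free.

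**What to change.** 1. Keep the one-month window for infection, urinary retention and bleeding.
2. Classify delayed healing at 3 months after surgery, from the wound-healing follow-up that the primary outcome already requires. State that follow-up of unhealed patients continues at least to that point.
3. Record recurrence beyond one month, at the outpatient follow-up and at the existing six-month contact. Alternatively, state plainly that recurrence is not assessed after one month and that no conclusion about it will be drawn.
4. Change the abstract and section 6(3) so that they give the same windows.

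Items 1, 2 and 4 cost little more than wording, since the data for delayed healing are already needed for the primary outcome. Item 3 costs more. Some patients may be lost by six months. That contact is described only as a questionnaire, so recurrence found there may rest on patient report or routine examination, without planned imaging. If that is the route taken, the protocol should say how recurrence is ascertained, identically in both arms. Neither the sample size nor the interventions need to change.
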